## Methods

Based on the findings of other large-scale CQI initiatives [72], this study will be based on a quasi-randomised cluster-controlled trial allowing for a comprehensive and rigorous evaluation of the proposed intervention [73]. Such a design has been used to better understand both processes and outcomes of CQI [51]. Within the province of Quebec, clinics from randomly selected health regions will receive the intervention, while others will serve as controls (no CQI intervention). Intervention clinics will be matched with control clinics. The matching will be based on the clinic level (1 to 10, based on the number of patients registered and services offered) [74]. Clinics in the control group will receive an audit on a selection of AA indicators (Table 1) and will be offered the intervention 12 to 18 months following their recruitment.

**Table 1 Tab1:** Definition of AA measures

Measure	Definition

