**Outcome**	
3rd next available appointment (weekly)	Number of days before the 3rd next available appointment open for general consultation
Relational continuity (monthly)	Total number of medical consultations with a patient’s attached family physician (or specialised nurse) out of the total number of consultations with any family physician (or specialised nurse) from the clinic. Evaluates relational continuity between the provider and their registered patients

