### Sample size justification

The Quebec CQI pilot project showed that the average time to the 3rd next available appointment (primary outcome) is 11 days (sd = 10). Forty-eight clinics (clusters) averaging 15 professionals per clinic for a total of 720 professionals over six measurement time points will be measured every week or month (depending on the measure). An assumed intracluster correlation (ICC) of 0.364 (from the pilot project) provides about 80% power to detect a small effect size of 0.25 (Cohen’s d, assuming that variation will increase over the course of the intervention). This translates into a 50% reduction in time to the 3rd next available appointment from the baseline assessment [83]. Variations in clinic size have been considered (coefficient of variation of 0.49 according to the pilot project) [84]. No inflation for loss to follow-up is planned because the data is readily obtained from the EMR system for all professionals. Provision for one interim analysis 12-months post recruitment is planned using the Demets and Lan’s alpha spending function approach [85]. Thus, we aim to recruit 48 PHC clinics (24 interventions and 24 controls) for the trial proposed in this study.

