The impact of the intervention on AA outcomes (Obj. 3) will be structured around the quintuple aim [116]. For all outcomes, we will describe clinics and participants using means and standard deviations or medians and interquartile ranges. Also, time series analyses will be performed based on EMR indicators to detect changes since baseline, at the beginning of the intervention (T3), during the intervention (T3–T18) and the sustainability of the changes (T30). *Care team functioning*: To account for clustering of providers within clinics, the primary outcome measure, 3rd next available appointment, will be analysed using a generalised linear mixed model (with log link and quasi-Poisson distribution) adjusting for time to account for secular trends as well as important contextual factors such as number of providers and readiness for change. We will inspect missing data, and if more than 10% of the sample has missing values, we will use multiple imputation techniques. Otherwise, the maximum-likelihood method of estimation is considered adequate to address missing data in such regression models [117, 118]. Differences between the control and intervention periods and time trends will be estimated using odds ratios and their 95% confidence intervals. Similar regression models will be used (as dictated by the distribution of the data) to assess differences in % of 48-h open slots, walk-in usage, relational continuity and multidisciplinary involvement. *Patient experience*: A comprehensive description of patients’ experiences will be generated three times over the study. Items that focus on ease of access, perception of interprofessional collaboration, satisfaction with the appointment process and consultations outside the clinic for non-urgent care will be used for longitudinal analysis purposes. *Population health*: Discontinuity for chronic patients will be analysed using a generalised linear mixed model to assess the impact of the project on the management of chronic patients. *Health equity and inclusion*: Accessibility and patient experience will be stratified by visible minority status, ethnicity, preferred language, gender and physical or mental ability. If any disparity seems apparent, this issue will be addressed during the improvement efforts. *Efficiency:* Total costs to the system related to the implementation of the intervention as well as costs per clinic and cohort, accounting for different organisational characteristics, will be calculated. We will analyse the QI coach’s logbook to assign costs to the different tasks performed. Incremental ratios (i.e. change in costs to use the intervention divided by change in the 3rd next available appointment) will also be calculated.

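### The primary effect is to be reported as odds ratios between periods, but the stated model on days gives ratios of mean days, and the trial compares parallel groups of clinics

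*Protocol article*

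**What the plan says.** Table 1 of the protocol article defines the primary outcome as "Number of days before the 3rd next available appointment open for general consultation". The Data analyses section says it will be analysed with a "generalised linear mixed model (with log link and quasi-Poisson distribution) adjusting for time to account for secular trends", together with contextual covariates. Two sentences on missing data follow, and then the effect measure: "Differences between the control and intervention periods and time trends will be estimated using odds ratios and their 95% confidence intervals". Only after that does the section turn to the secondary proportions, for which similar models are promised, chosen according to the distribution of the data.

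On design, the Methods section says that "clinics from randomly selected health regions will receive the intervention, while others will serve as controls (no CQI intervention"). The Sample size justification gives the allocation: "we aim to recruit 48 PHC clinics (24 interventions and 24 controls"). Control clinics "will be offered the intervention 12 to 18 months following their recruitment". The Data collection section promises at least 3 months of pre-intervention data, and mentions only the intervention group when it does so.

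**The concern.** One sentence fixes both the scale and the contrast of the primary result, and neither fits the rest of the plan.

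- **Scale.** An odds ratio compares the odds of an event. A number of days under a log-link count model has a mean but no event and no odds. The article therefore promises a quantity that its model does not produce. The sentence follows directly on the primary model and precedes the proportions, so it cannot be read as covering only the proportions.
- **Contrast.** Control and intervention periods are the vocabulary of a design in which each clinic passes through both conditions. The article describes concurrent groups and no crossover or stepped-wedge analysis. The Data analyses section names no group term or group-by-time term for the primary outcome, so this sentence is its only statement of what is compared with what.

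At stake are the meaning of the headline number and the assurance that two analysts working from the article would estimate the same quantity. The interim look for superiority uses the same outcome.

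**Working it through.** **1. What the stated model estimates.** With Y the days, G = 1 for intervention and 0 for control, f(t) the time adjustment and u the clinic effect:

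log E(Y) = b0 + b1·G + f(t) + u

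At the same time, covariates and clinic effect, exp(b1) = E(Y | G = 1) / E(Y | G = 0), a ratio of mean days. An odds ratio needs a probability p of an event and compares p/(1 − p). No such p appears in the model.

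**2. The plan's own effect sizes on that scale.** Inputs from the Sample size justification: mean 11 days, SD 10, Cohen's d = 0.25, and a 50% reduction from baseline.

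- A 50% reduction: 11 × 0.5 = 5.5 days; ratio 5.5/11 = 0.50.
- d = 0.25 at SD 10: 0.25 × 10 = 2.5 days; (11 − 2.5)/11 = 8.5/11 = 0.77.

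Both are ratios of means. The first is stated relative to baseline, not to the control group, and the two differ, so neither is taken here as the between-group target.

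**3. How far an odds ratio would lie from these.** This step is an illustration on assumptions, because the plan sets no cut-off. Take a negative binomial count with mean 11 and variance 100 and the same variance-to-mean ratio (100/11 = 9.09) in the comparison group. Compute the odds of exceeding a cut-off of c days.

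Example at c = 7: the probability of exceeding it is 0.538 at mean 11 and 0.255 at mean 5.5. The odds ratio is (0.255/0.745)/(0.538/0.462), which is 0.295 before rounding of the probabilities.

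| Cut-off (days) | Odds ratio when mean ratio is 0.50 | Odds ratio when mean ratio is 0.77 |
|---|---|---|
| 2 | 0.247 | 0.554 |
| 5 | 0.285 | 0.597 |
| 7 | 0.295 | 0.609 |
| 10 | 0.298 | 0.616 |
| 14 | 0.292 | 0.614 |
| 21 | 0.270 | 0.597 |

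The two measures are not interchangeable: 0.50 goes with about 0.25 to 0.30, and 0.77 with about 0.55 to 0.62.

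**4. The contrast, place by place.**

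- Methods: randomly selected regions receive the intervention and others are controls. This is a comparison of groups.
- Sample size justification: 24 versus 24 clinics, again groups.
- Research objectives, objective 2: study groups, intervention and control.
- Data analyses, effect sentence: periods.

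Only the last differs. The readings can diverge in practice. If collection runs 24 months from recruitment and a control clinic starts the intervention when offered it, at 12 to 18 months, then 24 − 18 = 6 to 24 − 12 = 12 months of its data would be control time under a group contrast and intervention time under an exposure contrast. Whether control data from after that offer enter the primary analysis is not stated.

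**The case against.** **The label is harmless.** Model, link and distribution are stated and suit days. Fitted as written, the exponentiated coefficient, its interval and its p-value are the same whatever the measure is called, and relabelling makes the result comparable with a percentage reduction. This stands as far as it goes: the scale error is one of reporting, not of estimation. It does not make the sentence right, and a reader who took a published odds ratio at its word would misjudge the effect.

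**Periods may mean exposure status.** Intervention clinics have pre-intervention months, controls are later offered the intervention, and the model adjusts for time. Clinics can therefore have unexposed and exposed periods, and the exact parameterisation is commonly left to an analysis plan. This also stands in part: the wording is ambiguous rather than plainly wrong. But the one contrast the article does name is not the one its design describes.

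**A stronger reading to avoid.** A reader might infer that the primary result will be an uncontrolled before-after comparison that absorbs secular change. The article does not support that. It adjusts for secular trends in the model sentence itself and nowhere says that control clinics are left out. Any figure for spurious change in days would need an assumed drift and an unadjusted analysis that the article does not describe.

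**Conclusion.** The point holds in two parts of unequal strength.

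- **Odds ratios: wrong as written.** The stated model on days gives ratios of mean days. This follows from the article's own outcome definition and model, and needs no assumption. The gap between the scales in the table does rest on an assumed distribution and assumed cut-offs, and only shows that the label is not neutral.
- **Periods: ambiguous and at odds with the parallel design.** It needs clarifying, but bias is not shown.

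A reader might also infer that the planned between-group effect is a mean ratio of 0.50. The article gives the 50% as a change from baseline, beside a standardised effect that works out at 0.77, so that inference is not secure. The point does not depend on the power claim and does not alter the number of clinics.

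**What to change.** Replace the effect sentence in Data analyses with: *The primary effect is the ratio of mean days to the 3rd next available appointment, intervention versus control clinics, adjusted for time, with 95% CI.*

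- If pre-intervention EMR data are also extracted for control clinics, estimate the effect from a group-by-time term. The article promises such data only for the intervention group, so this must be confirmed first. Without them, the time-adjusted group contrast still repairs the sentence.
- If an exposure-status contrast was intended, say so and state how control-clinic time after the delayed offer is counted.
- Keep odds ratios only for outcomes modelled with a logit link.

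The cost is one sentence. The sample size does not change. No new data are needed for the group contrast; the group-by-time version needs control-clinic baseline extraction if that is not already planned.

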### Data collection

Complementary qualitative and quantitative data will be collected over a period of 24 months. To evaluate the proposed trial objectives, data collection will be extended by 12 months *in the intervention group only*. We will collect data from all clinics in the intervention group for at least 3 months prior to the start of the intervention.

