
The AA process and outcomes of the intervention (Obj. 4) will be documented 12 months after the end of the intervention to assess the sustainability of its effects over time. Regression models similar to those used in objective 3 will be used to identify the factors that influence sustainability of the intervention effects. Factors such as team context, participation in each intervention activity, support duration (wave) and progress made during the intervention will be included in the model. The association between the sustainability of outcomes and each factor will be estimated using regression estimates and their 95% confidence intervals. We will also evaluate whether the practices put in place (processes) are maintained.

In addition to the analyses described above, one interim analysis will be conducted after 12 months of the intervention. This analysis will focus mainly on the trial’s primary outcome (3rd next available appointment) to identify early evidence of the intervention’s superiority. This study will be monitored by an independent Data Safety and Monitoring Committee (DSMC) formed by the steering committee. The DSMB will consist of an independent healthcare organization expert, a PHC physician and a statistician who are not involved in this study. The interim analysis will be performed by a statistician who is blind to the treatment allocation. Members of the DSMC will also be responsible for developing terms of reference, including stopping rules to be used during interim analysis. The steering committee will be notified by the DSMC only if the latter considers continuance of the study to be futile.

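### The interim look is planned, with alpha spending, to detect early superiority, but the DSMC may report only futility to the steering committee; the timing of the look is also worded in two ways

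*Protocol article*

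**What the plan says.** All statements are in the protocol article.

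- **Alpha spending and first timing** (Sample size justification): "Provision for one interim analysis 12-months post recruitment is planned using the Demets and Lan’s alpha spending function approach".
- **Second timing** (Data analyses, last paragraph): "one interim analysis will be conducted after 12 months of the intervention".
- **Purpose** (same paragraph): the look concentrates on the third next available appointment, "to identify early evidence of the intervention’s superiority".
- **Stopping rules** (same paragraph): "Members of the DSMC will also be responsible for developing terms of reference, including stopping rules to be used during interim analysis".
- **Notification** (same paragraph): "The steering committee will be notified by the DSMC only if the latter considers continuance of the study to be futile".

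Three other places bear on the timing. Data collection says that intervention clinics supply data "for at least 3 months prior to the start of the intervention". Data analyses puts the beginning of the intervention at T3 and its course at T3 to T18. The opening of Methods says that control clinics will be offered the intervention 12 to 18 months after they are recruited.

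**The concern.** An alpha-spending function is needed when an interim look can lead to an efficacy claim. Here the look has that purpose and that provision, but the reporting rule lets through only the opposite conclusion. If the DSMC saw a crossed superiority boundary, the rule as worded would keep it from the body that could act on it. If the DSMC reported futility, it would do so from a look for which the article states no futility purpose.

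The date of the look is a second, smaller matter. The two sections count the 12 months from different events. The choice affects how much exposure the intervention clinics have had, and whether control clinics may by then have been offered the same intervention.

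**Working it through.** **1. Purpose against permitted action**

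| Element | Superiority | Futility |
|---|---|---|
| Stated purpose of the look | yes | not stated |
| Alpha spending provided | yes | not needed for futility |
| Steering committee notified | no | yes |

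The two columns do not agree. The notification sentence carries no exception. Stopping rules written by the DSMC could define a superiority boundary, but the protocol's own sentence would still bar its report to the steering committee.

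**2. Type I error**

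If the final test uses the level left by the spending function, the overall error is at most 5%. If the superiority look is never acted on, that final level is below 5%, and a futility stop can only lower the error further. There is no inflation on either view.

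**3. Power cost if the superiority look cannot be acted on**

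Input from the article: power of about 80%. A single-time-point cluster calculation (24 clinics per arm, 15 professionals, ICC 0.364, coefficient of variation 0.49) gives 23% for d = 0.25. With six time points the result runs from about 24% to over 99%, depending on a correlation over time and a baseline adjustment that are not given. The 80% can be neither confirmed nor refuted, so it serves here only as a starting value.

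Assumptions not in the article: overall two-sided alpha 0.05, the spending function, and the information fraction t. If information is proportional to time over T3 to T18, a look at T12 gives t = (12 − 3)/15 = 0.60 and a look at T15 gives t = (15 − 3)/15 = 0.80. Half information is added as a lower value.

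Formulas:
- O'Brien-Fleming-type on total alpha: α₁ = 2[1 − Φ(1.960/√t)]
- O'Brien-Fleming-type with 0.025 per side: α₁ = 4[1 − Φ(2.241/√t)]
- Pocock-type: α₁ = 0.05 ln[1 + (e − 1)t]
- Interim bound c₁ = Φ⁻¹(1 − α₁/2). Final bound c₂ solves P(|Z₁| < c₁, |Z₂| < c₂) = 0.95, with correlation √t.
- Drift for 80% fixed-sample power: 1.960 + 0.842 = 2.802. Power at the final test alone: 1 − Φ(c₂ − 2.802).

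| Function | t | α₁ | c₂ | Final level | Power | Loss (points) |
|---|---|---|---|---|---|---|
| OBF, per side | 0.5 | 0.0031 | 1.969 | 0.049 | 79.8% | 0.2 |
| OBF, per side | 0.6 | 0.0076 | 1.981 | 0.048 | 79.4% | 0.6 |
| OBF, per side | 0.8 | 0.0244 | 2.025 | 0.043 | 78.1% | 1.9 |
| OBF, total alpha | 0.5 | 0.0056 | 1.979 | 0.048 | 79.5% | 0.5 |
| OBF, total alpha | 0.6 | 0.0114 | 1.999 | 0.046 | 78.9% | 1.1 |
| OBF, total alpha | 0.8 | 0.0284 | 2.052 | 0.040 | 77.3% | 2.7 |
| Pocock | 0.5 | 0.0310 | 2.201 | 0.028 | 72.6% | 7.4 |
| Pocock | 0.6 | 0.0354 | 2.231 | 0.026 | 71.6% | 8.4 |
| Pocock | 0.8 | 0.0432 | 2.260 | 0.024 | 70.6% | 9.4 |

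**4. Timing**

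Take recruitment as T0 (an assumption; the article does not define it) and the start of the intervention as T3.
- 12 months after recruitment: T12, with 12 − 3 = 9 months of intervention.
- 12 months of intervention: 3 + 12 = T15.
- Difference: 3 months. T15 lies inside the 12 to 18 month window in which controls are offered the intervention; T12 is at its opening.

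On the other clock, the abstract gives 18 months of intervention and the Qualitative component ends it at T18, which implies a start at 18 − 18 = T0. Both wordings then give T12 and coincide.

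**The case against.** The strongest reply has four parts.

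**The DSMC terms of reference may settle it.** They are not shown, and an article may leave stopping rules to a charter. That is fair for the rules themselves, and the unnamed spending function and boundary are not counted here. It does not remove a reporting restriction that the article states without exception.

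**Futile may be loose wording.** In a paragraph about superiority it could mean that continuing is pointless because the question is answered. This is possible but is not normal monitoring usage; if it is meant, the sentence still needs rewriting. The possibility does mean that this may be one badly drafted sentence. A reader might infer that alpha is spent with no possible benefit; that is stronger than the text allows.

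**The cost is small.** This stands for O'Brien-Fleming-type spending. A headline loss of 7 points or more would rest on a Pocock-type function that the article does not name.

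**The timing conflict is conditional.** This also stands. The 3-month gap needs recruitment at T0 and a start at T3, and the article also supports a clock on which the gap vanishes. EMR data for the lead-in might be extracted retrospectively, so a delay between recruitment and start is not established. A reader might further infer that a look at T15 would compare against treated controls and so produce false futility. The article says only that controls are offered the intervention, and expects a first improvement aim to take 3 to 9 months. No size can be put on such dilution.

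**Conclusion.** The inconsistency is real: as written, the reporting rule defeats the stated purpose of the look, and the only result it lets through is not a stated purpose. The case rests on that contradiction rather than on lost power. The cost is about 0.2 to 2.7 points from a nominal 80% with O'Brien-Fleming-type spending, given two-sided 5% and information of 0.5 to 0.8; it reaches about 7 to 9 points only if a Pocock-type function were chosen. Type I error stays controlled.

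The two timing statements also need reconciling. The gap is about 3 months on the T0 and T3 assumptions and may be nil on the other clock that the article supports. A claim of bias from treated controls is not supported.

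**What to change.** Before the interim data are seen:

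1. State whether the look is for superiority, futility or both.
2. Match the notification rule to that choice. If superiority is kept, the DSMC also notifies the steering committee when the boundary is crossed. If only futility is meant, drop the alpha spending and keep the full 5% for the final test.
3. Give one time origin and one date for the look in both sections, preferably before control clinics are offered the intervention, and reconcile the T3 start with the 18-month duration ending at T18.

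The cost is wording in the protocol and the DSMC charter; the sample size and data collection need not change. Doing this before the look matters, because a choice made after the interim results are known could not be shown to be independent of them.
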